### **2.4.4.2 Secondary Outcomes**

①Change from baseline in average number of migraine days per perimenstrual period over cycles 4-6(14).

Calculation methods:

Average number of migraine days per perimenstrual period over cycles 4-6 is calculated as the cycle average, equals the total of migraine days during perimenstrual period over cycle 4, cycle

5 and cycle 6 divided by 3.

② Change from baseline in average number of migraine days per outside perimenstrual period over cycles 1-3 and cycles 4-6(14).

Calculation methods of the average number of migraine days during outside perimenstrual period at different timepoints:

a. Average number of migraine days per outside perimenstrual period over cycles 1-3 is calculated as the cycle average, equals the total of migraine days during outside perimenstrual period over cycle 1, cycle 2 and cycle 3 divided by 3;

b. Average number of migraine days per outside perimenstrual period over cycles 4-6 is calculated as the cycle average, equals the total of migraine days during outside perimenstrual period over cycle 4, cycle 5 and cycle 6 divided by 3.

③ Change from baseline in mean migraine hours during perimenstrual period over cycles 1-3 and cycles 4-6(14).

Calculation methods of the mean migraine hours during perimenstrual period at different timepoints:

a. Mean migraine hours during perimenstrual period over cycles 1-3 is calculated as daily average, equals the total of migraine hours during perimenstrual period divided by number of migraine attacks over cycles 1-3.

b. Mean migraine hours during perimenstrual period over cycles 4-6 is calculated as daily average, equals the total of migraine hours during perimenstrual period divided by number of migraine attacks over cycles 4-6.

④ Change from baseline in mean migraine hours during outside perimenstrual period over cycles 1-3 and cycles 4-6(14).

Calculation methods of the mean migraine hours during outside perimenstrual period at different timepoints:

a. Mean migraine hours during outside perimenstrual period over cycles 1-3 is calculated as daily average, equals the total of migraine hours during outside perimenstrual period divided by number of migraine attacks over cycles 1-3.

b. Mean migraine hours during outside perimenstrual period over cycles 4-6 is calculated as

daily average, equals the total of migraine hours during outside perimenstrual period divided by number of migraine attacks over cycles 4-6.

⑤ Change from baseline in mean pain visual analogue scale (VAS) during perimenstrual period over cycles 1-3 and cycles 4-6(16).

Calculation methods of the mean VAS scores during perimenstrual period at different timepoints:

a. Mean VAS during perimenstrual period over cycles 1-3 is calculated as daily average, equals the total of VAS score during perimenstrual period divided by number of migraine attacks over cycles 1-3.

b. Mean VAS during perimenstrual period over cycles 4-6 is calculated as daily average, equals the total of VAS score during perimenstrual period divided by number of migraine attacks over cycles 4-6.

VAS is widely accepted as one of the major outcomes for headache intensity. VAS-Pain scales are 0 to 10 where 0 = no pain, 10= pain as bad as can be.

⑥ Change from baseline in mean pain visual analogue scale (VAS) during outside perimenstrual period over cycles 1-3 and cycles 4-6(16).

Calculation methods of the mean VAS scores during outside perimenstrual period at different timepoints:

a. Mean VAS during outside perimenstrual period over cycles 1-3 is calculated as daily average, equals the total of VAS score during outside perimenstrual period divided by number of migraine attacks over cycles 1-3.

b. Mean VAS during outside perimenstrual period over cycles 4-6 is calculated as daily average, equals the total of VAS score during outside perimenstrual period divided by number of migraine attacks over cycles 4-6.

⑦  $\geq 50\%$  migraine responder rate(14).

Calculation methods:

Proportion of participants with at least 50% reduction from baseline in number of migraine days during cycles 1-3 and cycles 4-6.

⑧ Intake of acute pain medication(14).

Calculation methods:

Proportion of participants using acute pain medication during cycles 1-3 and cycles 4-6.

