### **8.1 Statistical Analysis**

The primary study hypothesis is that acupuncture is different from medication in decreasing migraine days for women with MRM. The primary outcome is the change from baseline in average number of migraine days per perimenstrual period over cycles 1-3, assessed using headache diary data. The primary analysis will be intention-to-treat with the last observation carried forward (LOCF) method. Migraine days during perimenstrual period will be

summarized in each treatment group and compared using mixed-effect model.

The following secondary outcomes will be analyzed using the mixed-effect model, *t* test, Wilcoxon rank-sum test, Chi-square test or Fisher's exact test, as appropriate and the intent-to-treat principal:

1. Change from baseline in average number of migraine days per perimenstrual period over cycles 4-6
2. Change from baseline in average number of migraine days per outside perimenstrual period over cycles 1-3 and cycles 4-6
3. Change from baseline in mean migraine hours during perimenstrual period over cycles 1-3 and cycles 4-6
4. Change from baseline in mean migraine hours during outside perimenstrual period over cycles 1-3 and cycles 4-6
5. Change from baseline in mean pain VAS during perimenstrual period over cycles 1-3 and cycles 4-6
6. Change from baseline in mean pain VAS during outside perimenstrual period over cycles 1-3 and cycles 4-6
7. Proportion of participants with at least 50% reduction from baseline in number of migraine days during cycles 1-3 and cycles 4-6
8. Proportion of participants using acute pain medication during cycles 1-3 and cycles 4-6
9. Success rate of blinding at cycle 1.5 and cycle 3

A two-side test with  $p < 0.05$  will be considered significant for all analyses.

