## **Missing data**

Efficacy analyses will be conducted in the intention-to treat (ITT) set, which will include all randomized subjects of whom the migraine days are measured in at least on post-baseline 1 cycle.

Missing data will be imputed by the last observation carried forward (LOCF) method (2). In addition, to examine sensitivity of the LOCF method imputed the missing data, we will perform a sensitivity analysis with multiple imputation method under the missing at random (MAR) assumption (3) for the primary outcome with missing data. Multiple imputations use the observed data to fill in the missing values repeatedly to give rise to multiple “pseudo-complete” datasets. We will impute the missing data 100 times using the following one of methods 1) regression imputation, if data sets with monotone missing patterns, or 2) Markov chain Monte Carlo imputation, if data sets with other patterns. For this we will use the SAS procedure Proc MI process. Each method will give rise to 100 different imputed data sets. We will fit our final model described before to each of these imputed datasets and then compute an overall estimate of the intervention effect as an average of the imputation specific estimates. The standard error of the overall intervention effect estimate will be calculated using Rubin’s formula. SAS procedure Proc MIANALYZE will be used to implement these tasks.

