#### **6.3.4 Analyses for Secondary Outcome**

Efficacy analyses for all secondary outcomes will be performed in the ITT population observed cases, with imputation of missing data using LOCF method.

The mixed-effect model (using baseline value as a covariate, treatment as a fixed effect, and center as a random effect) will also be used for secondary outcomes of the changes from baseline in average number of migraine days per outside perimenstrual period, mean migraine hours during perimenstrual period and outside perimenstrual period, mean pain visual analogue scale (VAS) during perimenstrual period and outside perimenstrual period. For proportion of participants with at least 50% reduction from baseline in number of migraine days and proportion of participants using acute pain medication will be compared between groups using a Chi-square test or Fisher's exact test, as appropriate.

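### The per-attack formulas for migraine hours and VAS (secondary outcomes ③-⑥) cannot be validly computed as written: label and divisor disagree, the divisor is not tied to the window, and a woman with no attack has no value

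*Supplement*

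**What the plan says.** Protocol 2.4.4.2 gives each of outcomes ③-⑥ as a total divided by a count of attacks:

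- ③ perimenstrual hours: the mean "is calculated as daily average, equals the total of migraine hours during perimenstrual period divided by number of migraine attacks over cycles 1-3".
- ④ hours outside the perimenstrual period: "equals the total of migraine hours during outside perimenstrual period divided by number of migraine attacks over cycles 1-3".
- ⑤ perimenstrual VAS: "equals the total of VAS score during perimenstrual period divided by number of migraine attacks over cycles 1-3".
- ⑥ VAS outside the period, here for follow-up: "equals the total of VAS score during outside perimenstrual period divided by number of migraine attacks over cycles 4-6".

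All of them are labelled a daily average. Each is assessed over two spans, as in Protocol 8.1: "Change from baseline in mean pain VAS during outside perimenstrual period over cycles 1-3 and cycles 4-6". That makes 4 outcomes × 2 spans = 8 comparisons. The primary outcome and outcomes ① and ② instead divide a day count by a fixed 3.

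On absent values, SAP 6.3.1 (Missing data) states: "Missing data will be imputed by the last observation carried forward (LOCF) method". SAP 6.3.4 adds: "Efficacy analyses for all secondary outcomes will be performed in the ITT population observed cases, with imputation of missing data using LOCF method". The multiple-imputation sensitivity analysis is planned only "for the primary outcome with missing data". SAP 6.3.4 analyses ③-⑥ with a baseline-adjusted mixed model, which needs a number for every woman included. Neither document says what value a woman without attacks receives.

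**The concern.** One rule leaves three things open.

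1. **Label against divisor.** A daily average needs days in the denominator; the formula has attacks. The two differ whenever an attack touches more than one day.
2. **Window of the denominator.** In the sentence the window qualifies only the total and the cycles qualify only the attack count. The words for the denominator are the same in ③ and ④, although two different windows are meant.
3. **No attack.** The ratio is 0/0. Eligibility requires perimenstrual attacks in at least two of three cycles and non-menstrual migraine more than once a month, so this should be rare at baseline. It arises mainly after randomisation, among the women who do best, and possibly more often in one arm.

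At stake are eight comparisons, each tested at the 5% level without adjustment, whose results could depend on a choice that nobody has written down. No planned sensitivity analysis would show it.

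**Working it through.** **Step 1. The plan's own figure.** The documents give no power or sample size for ③-⑥. The one figure available is 68 per group for migraine days (Protocol 2.4.1.3): 3.1 (SD 2.7) vs 5.2 (SD 4.4) over 12 weeks, two-sided 5%, 90% power. The difference is 2.1 and the pooled SD is √((2.7² + 4.4²)/2) = 3.65. The normal approximation gives 64 and the t test 65. A t test with the Mann-Whitney efficiency factor 3/π gives 68 (power 0.902), but the protocol does not name the test. Allowing for 20% loss, 68/0.8 = 85, against 86 planned. These means and SDs are used below only to gauge how many women have no attack.

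**Step 2. Share of women with no attack.** Every attack produces at least one migraine day, so no migraine day means no attack. Assume a negative binomial with the protocol's mean m and SD s. Then k = m²/(s² − m), and P(0) = (k/(k + f·m))^k, where f is the share of days that falls in the window. The documents do not give f.

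- Acupuncture: k = 9.61/(7.29 − 3.1) = 2.29
- Medication: k = 27.04/(19.36 − 5.2) = 1.91

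| Assumption | Acupuncture | Medication | Women of 86 |
|---|---|---|---|
| f = 1 | 14.1% | 8.1% | about 12 vs 7 |
| f = 0.5 | 30.6% | 19.4% | about 26 vs 17 |
| Poisson, f = 1 (ignores the SDs) | 4.5% | 0.6% | about 4 vs 0 or 1 |

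**Step 3. What the handling rule does.** Assume equal per-attack duration in both arms: 20 h at baseline, 16 h on treatment, SD 8 h, correlation 0.5, 86 women per arm. Being attack-free is random within an arm, with the Step 2 shares. The comparison is baseline-adjusted, with 3,000 simulated trials. Any difference then comes from the rule alone.

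| Rule for a woman with no attack | Difference, f = 1 | Difference, f = 0.5 | Rejected at 5% |
|---|---|---|---|
| Left out (attackers only) | 0.0 h | 0.0 h | 4-5% |
| Baseline carried forward | +0.2 h | +0.5 h | 5-7% |
| Scored 0 h | −0.9 h | −1.8 h | 11-25% |

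Positive differences are against acupuncture. Hand arithmetic agrees. With f = 0.5 the shares differ by 0.306 − 0.194 = 0.112. Carrying 20 h forward instead of 16 h shifts the difference by 0.112 × 4 = 0.45 h. Scoring 0 shifts it by −0.112 × 16 = −1.8 h.

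**Step 4. Denominator.** Assume 3 perimenstrual attacks of 20 h in each period, while outside attacks fall from 6 to 3. With same-window attacks the perimenstrual mean is 60/3 = 20 h both times. With all attacks it goes from 60/9 = 6.7 h to 60/6 = 10 h: a rise of half with no perimenstrual change.

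**The case against.** The case for leaving the plan alone has several parts, and much of it stands.

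- **A reader might infer that the plan prescribes division by all attacks.** It does not say so. The sentence is elliptical: read equally strictly, the numerator has no cycle limit either. Sharing both qualifiers, so that attacks in the same window and cycles are counted, may well be what was meant. The text is ambiguous, and Step 4 shows only what the literal reading would do.
- **A reader might infer that attack-free women will be filled by LOCF.** That is an inference. LOCF applies to missing data, and a completed diary without attacks is not missing. But then no rule is left for the 0/0, and naming observed cases beside LOCF in SAP 6.3.4 does not settle it.
- **A reader might infer a known bias against the better treatment.** The documents do not support a direction. In Step 3 the carried-forward shift is small and leaving women out gives none, although the latter holds only because duration was assumed unrelated to being attack-free. A carried-forward value need not be worse either: for cycles 4-6 it could be the cycles 1-3 value.
- **The size is uncertain.** The pilot figures are days over 12 weeks, not attacks in a window, and the Poisson row is much lower.
- **Per-day burden is a different endpoint.** This stands too. The attack divisor is consistent across all eight formulas, and Protocol 2.4.4.1 has intensity recorded for each attack. A daily VAS with zeros on free days has no basis in the diary as described.
- **These are secondary outcomes.** The primary outcome, days divided by 3, is defined for any complete diary.

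None of this supplies a value for a woman without attacks or reconciles the label with the divisor.

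**Conclusion.** The concern holds as a fault of definition, not as proof of a wrong result. Outcomes ③-⑥ over two spans, eight comparisons in all, cannot be validly computed from the text. The label contradicts the divisor, the divisor's window is open, and women with no attack have no value.

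The gap is material. About 14% vs 8% of women would be affected if the 12-week counts cover the window, and about 31% vs 19% if half of the days do. Both pairs rest on the negative binomial assumption and the protocol's means and SDs. With equal true duration, the unwritten rule alone moves the estimate between about +0.5 h and −1.8 h, under the assumed durations. The direction depends on the rule chosen. The primary outcome and the sample size are not touched.

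**What to change.** Protocol 8.2 calls for a final SAP before database lock and code breaking, so amended wording at that point is enough:

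1. **Denominator and label.** Limit the attack count to the same window and the same cycles as the numerator, and call the result a mean per attack. Say how an attack that crosses the edge of the window is counted.
2. **No attack is not missing.** State that a migraine-free window with a completed diary is observed and is never imputed by LOCF. Reserve the missing-data rule for absent diaries, and resolve the observed-cases wording in SAP 6.3.4.
3. **An always-defined measure for hours.** Add total migraine hours in the window per observed cycle, with 0 for no attack, as the all-randomised comparison. Report per-attack hours and per-attack VAS as conditional on having an attack, and show the number of attack-free women by arm.

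The cost is wording and a re-derivation of hours from the attack start and stop times already in the diary. The downside is small: hours per cycle reflect burden rather than severity per attack and partly overlap with migraine days.

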#### ⑨ Blinding Assessment

To confirm the blinding of participants, a questionnaire of blinding test will be conducted for all participants in the middle of treatment phase (Cycle-1.5) and at the end of treatment phase (Cycle-3). Participants in the four centers will be asked to guess which group they had been allocated.

### **3. Safety Assessment**

All the serious adverse events (SAEs) and adverse events (AEs) will be recorded and measured by both participants themselves and clinicians including neurologists and acupuncturists through the whole trial. In our trial, the SAEs will be defined as events requiring hospitalization, causing disability or impaired ability to work, threatening life or resulting in death. AEs will be categorized as acupuncture related or medication related based on its potential association with acupuncture needling procedure by acupuncturists or medication intake procedure within 24 hours. The acupuncture related AEs defined as follows: broken needle, needle phobia, intense pricking, pricking lasting more than half an hour (no matter how intense it is) after acupuncture, hematoma, dermorrhagia, infection, abscess formation at the needling site, other discomfort induced by acupuncture (such as lassitude, numbness, somnolence, nausea, vomiting, palpitation, dizziness, headache, loss of appetite, insomnia, etc), and aggravation of existing symptoms, etc. Given that acupuncture is a minimally invasive therapy inevitably causing pain, pricking with a spontaneously remission within 30 min after acupuncture will be not regarded as acupuncture related AE. The medication related AEs defined as follows: nausea, palpitations, dyspepsia, upper abdominal pain, heartburn, somnolence, dizziness, and sweating attack, etc. The numbers of participants and events of AEs will be recorded. We will compare the proportion of participants who get treatment-emergent adverse events (TEAEs). Participants who get TEAEs at least once will be counted in for the comparison of the proportion.

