(Yanglingquan) for Shaoyang headache; LI4 (Hegu) and ST44 (Neiting) for Yangming headache; BL60 (Kunlun) and SI3 (Houxi) for Taiyang headache; LR3 (Taichong) and GB40 (QiuXu) for Jueyin headache; PC6 (Neiguan) for nausea and vomiting, and LR3 (Taichong) for dysphoria and susceptibility to rage. For premenstrual conditioning, each participant will have standard acupuncture points, KI12 (Dahe), CV3 (Zhongji) and ST29 (Guilai). All of the selected acupuncture points will be determined based on our previous research (16). After sterilizing the skin, the needle will be inserted 10 to 15mm in depth and manipulated by rotation methods to produce a characteristic sensation known as de qi (feeling of needle sensation refers to tenseness around the needle felt by the practitioner and numbness, distension, soreness, and heaviness around the point felt by the patient) at each point. Ten to twelve sterile disposable steel needles in each session will be used for acupuncture.

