#### **4.2 Treatment of medication group**

In the medication group, participants will be given naproxen sustained release tablets (Diao Group Chengdu Pharmaceutical LTD, Chengdu, China) plus sham acupuncture. Naproxen sustained release tablets will be taken with a peri-menstrual dosing strategy (250mg/tablet, 2 tablets each time, once per day), which will start three days before each predicted onset of the menstruation and continue until the end of their menstrual cycle for 3 cycles. In the event that menstruation begins later than predicted, no adjustment to the treatment will be made. If the MRM occurs earlier than predicted, participants will be asked to begin taking naproxen immediately and one day earlier in the next cycle in an attempt to provide prophylactic coverage. The timing of treatment will be based on information collected (a headache diary) during the baseline phase and will not account for variability in menstruation and migraine onset during the treatment phase.

The method of applying blunt needles on effective acupuncture points will be not used in this trial as control for following reason: patients in China are very familiar with the sensations caused by acupuncture and therefore they may easily identify the blunt needles.

To make the needling stimulation consistent, the same type, size, and number of needles will be used for both groups. In order to avoid possible therapeutic effects of sham acupuncture,

the non-effective acupoints are chosen by the following three rules: (1) Acupuncture points that are defined as unrelated to headache or menstruation based on a vast amount of Chinese medicine reference books (26 ancient Chinese books of acupuncture, three Chinese acupuncture textbooks and >100 acupuncture research literatures); (2) 15 acupuncture points in the vicinity of elbow and knee joints are selected while the acupuncture points on the head, hands, feet, and trunk are excluded; (3) To mimic the nature of selecting points based on syndrome differentiation, the 15 sham points in the vicinity of elbow and knee joints are further randomly assigned to 3 subgroups: B, C, D. Each subgroup will have two points on the arms and three points on the legs. The participants in the medication group will be further randomly assigned into one of these three subgroups via central randomization system. Participants will be treated individually to avoid communication on the treatments they received.

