### **7.4 Medical Coding**

A data administrator who has the medicine background will take charge of the medical coding. The contents of the coding are the clinical history, adverse events, and combined medication. The clinical history and adverse events will be coded through MedDRA dictionary (Version 13.0), and the combined medication will be coded via WHO DD dictionary (Version 2007.03). The lead researchers will verify the coded e-files.

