#### **6.3.5 Safety Analyses**

##### **Adverse events**

All adverse events and serious adverse events will be listed. Adverse events include the acupuncture-related adverse events and medication-related adverse events. Chi-square test or Fisher's exact test will be used to compare the incidence of adverse events between the acupuncture group and medication groups.

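### The one clearly stated between-arm harm comparison pools needle-type and drug-type events into any TEAE, which can dilute or cancel differences by event type; no estimate by type is clearly planned

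*Supplement*

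**What the plan says.** Protocol section 3 (Safety Assessment) first classifies events: "AEs will be categorized as acupuncture related or medication related based on its potential association with acupuncture needling procedure", or with tablet intake, within 24 hours. It records numbers of participants and of events. It then states one between-arm comparison, the proportion of women with treatment-emergent adverse events (TEAEs), and fixes the counting rule: "Participants who get TEAEs at least once will be counted in for the comparison of the proportion".

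SAP 6.3.5 says that all adverse events and serious adverse events will be listed and that adverse events include both the acupuncture-related and the medication-related kind. A chi-square or Fisher test will then "compare the incidence of adverse events between the acupuncture group and medication groups". No test or estimate by category, coded term or severity is spelled out.

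On exposure, protocol 4.1 gives the acupuncture arm true needling plus placebo tablets, and 4.2 gives the medication arm sham needling plus naproxen. Section 4.2 states that "the same type, size, and number of needles will be used for both groups", and section 4.1 that "Ten to twelve sterile disposable steel needles in each session will be used for acupuncture". Protocol 7.4 has adverse events coded in MedDRA. SAP 3.1 names safety, alongside efficacy, as something the trial is to demonstrate.

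**The concern.** In a double-dummy trial the two arms share much of their exposure. Both are needled repeatedly, and section 3 counts hematoma, dermorrhagia and pricking that lasts over half an hour as adverse events. A once-per-woman count of any event mixes these with the events by which naproxen and placebo tablets might differ, such as dyspepsia, upper abdominal pain and heartburn. A woman who already has a needle event cannot be counted again for a drug-type event.

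There are two possible consequences. If needle events are about equally common in both arms, they dilute a drug-type difference and usually add variance. If true needling produces more needle events and naproxen more systemic events, the two differences pull the pooled proportion in opposite directions and can cancel. In either case the one comparison that is clearly pre-specified could be unremarkable although the arms differ in the kind of harm they carry.

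**Working it through.** **What the documents supply.** They give 86 women per arm (protocol 2.4.1.3), 1:1 allocation (protocol section 11, Table 1), a two-sided 5% level (SAP 6.3.1, Analysis Software) and no multiplicity adjustment for safety (SAP 6.3.1, Multiple Comparisons). They give no expected adverse event rate and no power for safety, so there is no figure of the plan's own to reproduce on this point. All event rates below are assumptions.

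**Dilution.** Let q be the proportion with a needle-type event, the same in both arms, and p the proportion with a drug-type event, independent of the first. The any-event proportion is

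1 − (1 − q)(1 − p).

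The difference between arms is then (1 − q) × (p_med − p_acu), so a shared rate q shrinks the drug-type difference by the factor (1 − q).

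The example takes p = 5% (acupuncture arm) versus 20% (medication arm), with exact binomial power of the Pearson chi-square test at 86 per arm:

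| Shared needle rate q | Any event, acupuncture arm | Any event, medication arm | Difference (points) | Power |
|---|---|---|---|---|
| none (drug-type compared alone) | 5.0% | 20.0% | 15.0 | 88% |
| 5% | 9.8% | 24.0% | 14.3 | 71% |
| 10% | 14.5% | 28.0% | 13.5 | 59% |
| 25% | 28.8% | 40.0% | 11.3 | 34% |
| 40% | 43.0% | 52.0% | 9.0 | 23% |

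For q = 10%: 1 − 0.90 × 0.95 = 14.5% and 1 − 0.90 × 0.80 = 28.0%, a difference of 13.5 points. The difference shrinks modestly when q is small. Power falls faster because the binomial variance also rises as the proportions move away from zero.

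With drug-type rates of 5% versus 15%, power is 61% alone and 42%, 32%, 18% and 13% at q = 5%, 10%, 25% and 40%.

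**Is a q in this range conceivable?** At two sessions a week for about 12 weeks, 24 sessions × 10 to 12 needles = 240 to 288 insertions per woman. At r reportable needle events per insertion, independent across insertions, the proportion with at least one is 1 − (1 − r)^k:

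- r = 0.5 per 1000: 11% to 13%
- r = 1 per 1000: 21% to 25%
- r = 2 per 1000: 38% to 44%

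These values of r are assumed too. Clustering of events in women who bruise easily would lower the proportions.

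**Cancellation.** Now let the needle-type rates differ: 20% in the acupuncture arm and 5% in the medication arm, with drug-type events at 5% and 20%.

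- Acupuncture arm: 1 − 0.80 × 0.95 = 24%.
- Medication arm: 1 − 0.95 × 0.80 = 24%.

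The pooled difference is zero, and the pooled test rejects only at its error rate of about 5%. Each event type compared alone has 88% power. With needle-type rates of 30% versus 15% instead, the pooled rates are 1 − 0.70 × 0.95 = 33.5% and 1 − 0.85 × 0.80 = 32.0%.

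**Would the two attribution categories be enough?** Not by themselves. Section 3's acupuncture list includes general symptoms ("such as lassitude, numbness, somnolence, nausea, vomiting, palpitation, dizziness, headache, loss of appetite, insomnia, etc"). Nausea, palpitation, somnolence and dizziness appear on the medication list as well. The same symptom can therefore fall in either category depending on which component is blamed, and a comparison by attribution would split it.

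**The case against.** A reader might infer that the pooled test largely hides any difference due to naproxen or to true needling. The documents do not support that. They give no event rates, and at a shared needle rate of 5% to 10% the visible difference loses only 5% to 10% of its size.

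The equal needle rate in both arms is also an assumption. Needle type, size and number are matched, and protocol 2.4.1.2 says the sham will give the same stimulation. But sham points lie near the elbow and knee, true points include the head and lower abdomen, and depth and rotation to de qi are described only for true needling (protocol 4.1 and 4.2). This weakens the dilution example. It does not remove the problem, because unequal needle rates are what make cancellation possible.

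It is also true that differences by type would not vanish. Events are categorised, participants and events are counted, and everything is listed. SAP 6.3.1 promises numbers and percentages for categorical variables and sets chi-square or Fisher as the general method. SAP 6.3.5 names the two categories just before its test, so it could be read as testing each. That reading is possible but not stated, and section 3 defines its comparison as any TEAE. A listing carries no planned estimate or confidence interval.

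Finally, the trial is sized for migraine days and both objectives name efficacy. Nothing says that the safety conclusion will rest on the pooled p-value, so it would be speculation to say that a real excess will be reported as no difference. An overall any-TEAE proportion is a normal headline measure and should stay.

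**Conclusion.** The point holds in a limited form. The only between-arm harm comparison clearly stated is a pooled, once-per-woman proportion. In this design it can dilute a component-specific harm or cancel opposite harms, and no estimate by event type is clearly planned. The size is unknown because it depends on rates the documents do not state. The fall in power from 88% to 71%, 59% or 34%, and the 24% versus 24% case, are illustrations. They rest on assumed rates, on independence of the two event types and, for the dilution figures, on an equal needle-event rate in both arms. This is an inexpensive improvement to a safety analysis that can already show imbalances descriptively. It is not evidence that a harm would be missed.

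**What to change.** Keep the overall TEAE proportion. In protocol section 3 and SAP 6.3.5, add by arm the number and percentage of women with at least one TEAE, with the risk difference and its 95% confidence interval, for two groups:

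- (a) needle-site events: hematoma, dermorrhagia, persistent pricking, and infection or abscess at the site;
- (b) gastrointestinal and other systemic events.

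Form the groups from MedDRA terms regardless of which component was blamed, since the attribution lists overlap. State that safety will be interpreted from (a), (b) and the pooled result together.

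The cost is SAP wording and one table from data already recorded and coded. The downside is two more safety comparisons without multiplicity adjustment, in line with what SAP 6.3.1 already accepts for safety outcomes.
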